**Fig. 2 Fig2:**
[figure not shown]
Intraoperative images of hybrid ablation. Left panel: left-sided thoracoscopic view of ablation of the left pulmonary veins using a bipolar clamp. Right panel: voltage map (Carto) after completion of the epicardial box lesion showing an isolated posterior left atrial wall. LAA left atrial appendix, PV pulmonary vein

The epicardial surgical ablation procedure is followed by transvenous endocardial validation of exit and entrance block of the pulmonary veins and the box lesion following a single-step procedure. The same techniques used during the transvenous catheter ablation are applied to this part of the hybrid procedure. In case of incomplete lesions, conductions gaps are completed endocardially. In case of a documented right AFL, AFL induced during ablation, or a dilated right atrium (> 25 mL/m^2^ in men, > 21 mL/m^2^ in women), a CTI line is performed endocardially. Additional endocardial lesions can be added, if necessary, at the hybrid physician’s discretion. If the patient is still in AF at the end of the procedure, the patient is electrically or pharmacologically cardioverted.

### Follow-up

Patients are seen at the outpatient clinic 3, 6, 12, 24, and 36 months after the predefined ablation procedures. At all visits the heart rhythm will be determined according to the HRS/EHRA/ECAS expert statement [24], which includes an ECG in case of symptoms and at each visit, 24-h Holter examination at 3 and 6 months, and a 7-day Holter examination at the remaining visits. Furthermore, in case of an absence of symptoms on the ECG, Holter examinations are performed. The Holter examinations are assessed by nonblinded but independent Holter specialists. At 12 and 36 months, quality of life (using the EQ-5D-5 L questionnaire) is re-assessed (Fig. 3). The SPIRIT checklists are presented in Fig. 4 and Additional file 1.

**Fig. 3 Fig3:**
[figure not shown]
Study flow chart. *A decision for a second ablation > 6 months after the index procedure, and a third ablation at any time are considered a failure. **A second procedure is always considered a failure. The primary endpoint is set at 12 months after the predefined ablation procedure(s). QOL quality of life

**Fig. 4 Fig4:**
[figure not shown]
SPIRIT figure. CT computed tomography, ECG electrocardiogram

### Cost-effectiveness

The economic evaluation will examine the cost-effectiveness of hybrid AF ablation compared with (repeated) transvenous endocardial catheter ablation from a societal perspective with a time horizon up to 36 months. The outcome measure will be the incremental costs per quality-adjusted life year (QALY) gained. To calculate the QALY, a generic health-related quality of life questionnaire, the EQ-5D-5 L, will be administered at baseline and at 12 and 36 months. The Netherlands tariff will be used to value the health states as experienced by patients [25].

All resource use related to both procedures within the hospital will be recorded. In addition, medical consumption of patients during follow-up will be recorded using the iMCQ, while productivity loss will be obtained using the iPCQ [26, 27]. For the valuation of resource use, unit prices will be derived from the Pharmacotherapeutic Compass, the Netherlands guidelines for cost calculation [28], and the hospital financial department.

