## Methods

### Design and hypothesis

This is a prospective, randomized trial conducted at the Maastricht University Medical Centre, Maastricht, the Netherlands. The study objective is to compare the efficacy and safety of two interventional approaches for symptomatic, drug refractory persistent or longstanding persistent AF. A total of 40 eligible patients will be randomized (in a 1:1 ratio) to the following treatment arms: 1) a hybrid ablation arm (*n* = 20 patients), a one-stage hybrid procedure consisting of surgical thoracoscopic epicardial ablation combined with endocardial catheter ablation; or 2) a catheter ablation arm (*n* = 20 patients), consisting of conventional endocardial catheter ablation, followed by repeated catheter ablation if clinically indicated and decided within 6 months after the initial procedure.

The primary and secondary effectiveness endpoints are shown in Table 1. A blanking period of 3 months is applied. A second ablation after the hybrid ablation and a decision for redo-ablation beyond 180 days after the index catheter ablation will be considered a failure. A third catheter ablation at any time will also be considered a failure in the catheter arm. While the current guidelines define failure as a recurrence of > 30 s, failure in the primary endpoint of this study is defined as a recurrence of > 5 min [19, 21]. This allows us to reliably evaluate various Holter examinations and this reflects a more clinical endpoint compared with > 30 s, since it has been shown that the presence of AF episodes >30 s do not predict clinically meaningful AF, and that quality of life is mainly negatively influenced in patients with a high symptomatic AF burden [22, 23]. The primary and secondary safety endpoints are shown in Table 2.

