
One reason for the inconsistent results and high failure rates might be the limitations of the devices used to create transmural lesions. For example, in the STAR-AF II trial standard unipolar endocardial uniparietal catheter techniques were used, which are known to not reliably produce long-lasting transmural lesions [38]. Incomplete linear lesions can be arrhythmogenic due to the possibility for re-entry at the site of gaps or by changing conduction velocity [39]. However, even if current state of the art technology is applied, as in the recent Fire and Ice trial, the limitations of endocardial ablation in reliably creating transmurality currently still remain evident [40]. Surgical bipolar and biparietal devices are better at creating transmural lesions, and modern technologies allow for an anatomical approach using thoracoscopic visualization. However, epicardial surgical ablation is unable to create efficacious isthmus lesions and lacks the opportunity of sophisticated high-density three-dimensional mapping and consecutive endocardial touch-up of gaps. A hybrid ablation, which encompasses all of these opportunities, can lead to single-procedure success rates of more than 85% freedom from AF without AADs [18, 30, 31].

Besides efficacy in terms of rhythm control, safety also determines if an approach can be recommended. The advantages of catheter ablation are that full sedation is not needed, the duration of admission is short, and recovery is fast. The complication rates of this procedure vary from 0.2% to 4% per complication, with a cumulated complication risk of 7.7% to 13% [32, 41], which we have confirmed in our center. A hybrid ablation gives a total minor complication rate of 4% and total major complication rate of 5% [42]. In our center, we have confirmed these reported complication rates [30].

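### EQ-5D-5L is taken only at baseline, 12 and 36 months, so the 36-month QALY rests on no utility measurement during the first year, when surgical recovery and the catheter-arm redo fall

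*Protocol article*

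**What the plan says.** The Cost-effectiveness section defines the economic result: "The outcome measure will be the incremental costs per quality-adjusted life year (QALY) gained", "with a time horizon up to 36 months". For the utilities, the EQ-5D-5L "will be administered at baseline and at 12 and 36 months". Pre-procedural investigations places the first questionnaire at baseline, and Follow-up gives the rest: "At 12 and 36 months, quality of life (using the EQ-5D-5 L questionnaire) is re-assessed". The three sections agree.

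Follow-up also sets the visit schedule: "Patients are seen at the outpatient clinic 3, 6, 12, 24, and 36 months after the predefined ablation procedures". The 3-, 6- and 24-month visits thus carry no utility measurement.

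Two statements elsewhere bear on the first year. In the catheter arm, the index ablation is "followed by repeated catheter ablation if clinically indicated and decided within 6 months after the initial procedure". The Discussion lists as advantages of catheter ablation that "full sedation is not needed, the duration of admission is short, and recovery is fast". The hybrid arm has thoracoscopic surgery under general anesthesia.

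**The concern.** A QALY total is the area under a patient's utility curve. With points at 0, 12 and 36 months, the shape of the curve inside the first year has to be assumed. Under the usual straight line, a change that begins and ends between two points adds exactly nothing, and a gain reached early is credited as if it built up slowly to month 12.

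The arms differ by design inside that window: one has surgical recovery, and only the other may have a permitted second procedure. The Design and hypothesis section itself links quality of life to a high burden of symptomatic AF, so utility can be expected to move around recurrence and redo.

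At stake is the incremental QALY, the denominator of the cost-effectiveness ratio. The planned bootstrap describes sampling uncertainty, not interpolation error. The planned multiple imputation fills in missed questionnaires; it cannot supply a time point scheduled for nobody.

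**Working it through.** **Plan's own figures.** The protocol gives no utility or QALY figure to reproduce. Its sample size (35% vs 83%, α = 0.05, 90% power) does reproduce at 20 per group, two-sided and without continuity correction (power 90.2%), but has no bearing on this point.

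**Inputs from the protocol.** Utilities at 0, 12 and 36 months; visits at 3, 6, 12, 24 and 36 months; horizon 36 months.

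**Assumed inputs.** All utility changes and their timing. Values are undiscounted, and straight-line interpolation is used because the article does not state a method.

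**Longest unmeasured interval.** Before month 12: 12 months as planned, 6 months with the existing visits (gaps of 3, 3 and 6). After month 12: 24 months as planned, 12 with the 24-month visit.

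**Formula.** QALY = Σ (tᵢ₊₁ − tᵢ) × (uᵢ + uᵢ₊₁)/2 ÷ 12, with t in months and u the change from baseline.

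*A. Gain g reached linearly by month 3 and held to month 36*
- True: g × (1.5 + 33)/12 = 2.875g
- Planned points: g × (6 + 24)/12 = 2.5g
- Missed: 0.375g, or 0.375/2.875 = 13%
- Six points (0, 3, 6, 12, 24, 36): 2.875g, so nothing is missed

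*B. Dip of depth d peaking at month 6, running from month 3 to month 9*
- True loss: d × 6/2/12 = 0.25d
- Planned points: 0
- Six points: d × (1.5 + 3)/12 = 0.375d, so the dip is seen but overstated

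*C. Post-procedure dip of depth d, recovering linearly by month 3*
- True loss: d × 3/2/12 = 0.125d
- Planned points: 0. Six points: 0

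| Scenario | Assumed change | True QALY | Planned | Six points |
|---|---|---|---|---|
| A, early gain | 0.05 / 0.10 / 0.20 | 0.144 / 0.288 / 0.575 | 0.125 / 0.250 / 0.500 | 0.144 / 0.288 / 0.575 |
| B, dip at month 6 (loss) | 0.05 / 0.10 / 0.20 | 0.013 / 0.025 / 0.050 | 0 | 0.019 / 0.038 / 0.075 |
| C, dip gone by month 3 (loss) | 0.05 to 0.30 | 0.006 to 0.038 | 0 | 0 |

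For changes of 0.05 to 0.20, the planned schedule misses 0.019 to 0.075 in A, 0.013 to 0.050 in B and 0.006 to 0.025 in C: about 0.01 to 0.08 QALY per affected patient.

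**Direction between arms (illustration).**
- If an early gain of 0.10 occurs only in successes at the planning rates, the missed difference is (0.83 − 0.35) × 0.0375 = 0.018, which understates hybrid.
- A redo dip of 0.10 in a share 31/70 of catheter patients (the centre's own series in the Discussion) is 0.025 × 31/70 = 0.011, which also understates hybrid.
- A surgical dip in every hybrid patient overstates hybrid by 0.0125 if its depth is 0.10, or by 0.0375 if 0.30.
- Net: 0.018 + 0.011 − 0.0125 = +0.017, or 0.018 + 0.011 − 0.0375 = −0.009. The sign depends on the assumption.

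**Clock.** Visits are counted from the predefined procedure or procedures. If the questionnaire follows that clock, a redo near month 6 puts the 12-month EQ-5D about 6 + 12 = 18 months after the index procedure, and the first gap lengthens in the catheter arm only.

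**The case against.** The strongest reply is that nothing here is contradictory: the sections agree, three measurements are a legitimate choice, and the economic evaluation is additional to the primary endpoint. The utility changes above are assumed. Losses in opposite arms partly cancel. A lasting rhythm difference, the only between-arm difference that the protocol quantifies, would still show at 12 and 36 months. With 20 per arm and an assumed 3-year QALY standard deviation of 0.3 to 0.6, the standard error of the difference is SD × √(2/20), about 0.09 to 0.19, larger than the amounts at issue.

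Most of that stands and limits the point. It does not remove it: interpolation error is not reflected in the reported interval, and utilities never collected cannot be recovered by any analysis plan.

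Four stronger readings are tempting and not supported:
- **That the strategies differ most in the early period.** The protocol offers only qualitative support (fast catheter recovery, surgery in one arm, redo in the other) and no figure.
- **That the schedule favours one arm.** The illustration above changes sign within plausible assumptions.
- **That using the existing visits would capture surgical recovery.** A dip over within 4 to 8 weeks scores zero under both schedules. If visits are re-timed after a redo, symptoms before the redo could also be missed.
- **That imputation can fill the early points for everyone already past those visits.** It can help only where enough other patients are measured at the same time point.

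**Conclusion.** The point holds as a limitation of the economic evaluation. The 36-month QALY uses no utility between baseline and month 12, although visits at 3 and 6 months already exist, and only one utility point after that until month 36. Under assumed changes of 0.05 to 0.20, about 0.01 to 0.08 QALY per affected patient goes uncounted; for an early sustained gain this is 13% of the true amount. Averaged over an arm the effect is smaller, and the net direction is undetermined. These sizes rest on assumed utilities, straight-line interpolation and no discounting. The primary endpoint is unaffected. The change is worth making because it is cheap and the data cannot be obtained later.

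**What to change.** 1. Administer the EQ-5D-5L also at the 3-, 6- and 24-month visits, in both arms, for all patients not yet past them.
2. Record the date of each questionnaire. Compute QALYs as the area under the curve through all points, on time since the index procedure (or randomization) in both arms, so that a redo does not shift the time scale in the catheter arm.
3. Where visits are re-timed after a redo, keep the 3- and 6-month questionnaires counted from the index procedure.
4. State as a limitation that a post-surgical dip resolved before month 3 remains unmeasured, and examine it in the planned sensitivity analysis with assumed decrements (for example 0.05 to 0.30, which gives 0.006 to 0.038 QALY per affected patient).

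Cost: three more short questionnaires per patient, at most 3 × 40 = 120 in all, and a minor amendment. Recruitment had started before the article was submitted, so patients already past a visit will lack that point. Multiple imputation can cover them only if enough others are measured there; the number observed at each time point should be reported.

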### Sample size calculation

The estimated success rate (freedom from any supraventricular arrhythmia lasting > 5 min without the use of Vaughan-Williams class I or III AAD through 12 months of follow-up after the last procedure) based on literature and our own clinical experience is 35% for single catheter ablation [2, 29] and 83% for a hybrid ablation [30, 31]. With a significance level of α = 0.05, and a power of 90%, 20 patients per group need to be included.

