Due to the complexity of the underlying pathology, nonparoxysmal forms of AF are challenging to treat. Endocardial PVI results in single-procedure success rates of 23–48% in this patient subgroup [1–5]. However, with a second procedure and the use of AADs, outcomes can be improved to 46–69% [1–4, 33]. While PVI is still the cornerstone of the treatment of any type of AF, the appropriate substrate modification approach for nonparoxysmal AF is controversial. While the addition of CFAE ablation to PVI improved outcome in the STAR-AF I trial (74% vs. 48%, *p* = 0.004), neither the STAR-AF II trial (59% vs. 49%, *p* = 0.15) nor a large meta-analysis of 1415 patients (29.7% vs. 31.3%, *p* = 0.17) could confirm this benefit [4–6]. Furthermore, the stepwise approach consisting of PVI followed by disconnection of caval veins, CFAE ablation, and linear ablation of the roof and mitral isthmus until sinus rhythm is restored showed inconsistent results [11–15, 34]. In addition, it has been shown that full endocardial ablation of the posterior wall, which includes the application of linear lesions, does not always improve outcomes [7]. Other techniques exist, such as focal impulse and rotor modulation and isolation of low voltage areas, but without definitive positive results. In our experience, out of a total of 70 initial RF catheter ablations, performed between 2012 and 2015, 60 patients suffered from persistent AF and 10 from longstanding persistent AF. In 54 patients, only PVI was performed (77%), while in the remaining patients AT ablation (2%), CTI line (17%), and/or CFAE ablation (4%) was added. The median follow-up period was 21 months (range 15–30 months). The single-procedure success rate was disappointing, with only 21% of patients being free of supraventricular arrhythmias without AADs, and 27% with the use of an AAD. In 31/51 recurrences, a redo-procedure was performed, of which five were His bundle ablations. The pulmonary vein reconduction rate was 70% of all pulmonary veins. After the redo-procedure, the success rate without the use of AADs improved to 43%, and with the use of an AAD to 48%. The variety of reported success rates has led to different recommendations in consensus documents and guidelines. The most recent ESC guidelines do not recommend more extensive endocardial ablation during a first ablation attempt since there is not enough evidence to justify the prolonged procedure and radiation times, and the possibly higher complication rates (class IIa) [32]. On the other hand, the 2017 HRS/EHRA/ECAS expert consensus states that posterior wall isolation using a superior and inferior line in catheter ablation of nonparoxysmal AF may be considered (class IIb) [19]. In the surgical community, consensus has been achieved that additional lesions in minimally invasive off-pump procedures for nonparoxysmal AF are recommended [20] since PVI alone does not achieve outcomes comparable to minimally invasive versions of the on-pump maze procedure (60% vs. > 80%) [35–37]. Therefore, we decided to apply the same lesion set consisting of PVI and isolation of the posterior atrial wall (a so-called box lesion) in both arms of this study.

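### The 90% power rests on a single-procedure catheter success rate of 35%, but the catheter arm is scored after an allowed second ablation

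*Protocol article*

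**What the plan says.** The section on sample size calculation defines success as freedom from supraventricular arrhythmia without a class I or III "AAD through 12 months of follow-up after the last procedure". In the same sentence it sets the expected rates at "35% for single catheter ablation [2, 29] and 83% for a hybrid ablation [30, 31"]. It concludes: "With a significance level of α = 0.05, and a power of 90%, 20 patients per group need to be included". It states neither the test nor whether alpha is two-sided.

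The catheter arm is not a single-procedure arm. The section on design and hypothesis describes it as conventional endocardial ablation "followed by repeated catheter ablation if clinically indicated and decided within 6 months after the initial procedure". The abstract says that a second procedure planned within that window may count towards the primary endpoint. According to the design section and the legend of Fig. 3, only a redo decided later, or a third ablation, is a failure in this arm. In the hybrid arm any second ablation is a failure.

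The Discussion reports catheter results with and without a redo:

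- **Literature, single procedure:** 23–48%.
- **Literature, repeated:** "with a second procedure and the use of AADs, outcomes can be improved to 46–69" per cent.
- **Own centre (70 initial ablations), single procedure without drugs:** 21%.
- **Own centre, repeated:** "After the redo-procedure, the success rate without the use of AADs improved to 43" per cent.

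**The concern.** A power statement should describe the comparison that is randomized. Here the control strategy is one catheter ablation plus a second if indicated and decided in time, yet the control rate is labelled as that of a single ablation. The redo allowance can raise success only in the catheter arm. If it does, the planned difference of 48 points (83 − 35) is too large and the true power is below 90%.

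The calculation is the only stated justification for 40 patients. A reader of the eventual result, above all of a non-significant one, would take it to come from a test with a 10% chance of missing the assumed effect. That chance may be considerably higher.

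**Working it through.** **Inputs.** Hybrid 83%, catheter 35%, alpha 0.05, power 90% and 20 per group come from the sample size section. The chi-square test for categorical variables comes from the statistical analysis section. Two-sided testing without continuity correction is an assumption, made because it reproduces the stated number.

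**Step 1: reproduce the plan's figure.** With p̄ the mean of the two rates,

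n = [1.96·√(2p̄(1−p̄)) + 1.2816·√(p₁(1−p₁) + p₂(1−p₂))]² / (p₂−p₁)²

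For 0.35 and 0.83, p̄ = 0.59. The two terms in the bracket are 1.363 and 0.778, so n = (2.141)² / 0.48² = 19.9, rounded up to 20 per group.

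Power at n = 20 is Φ{[(p₂−p₁)√n − 1.96·√(2p̄(1−p̄))] / √(p₁(1−p₁) + p₂(1−p₂))} = Φ{(2.147 − 1.363)/0.607} = Φ(1.290) = 90.2%.

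The stated size therefore follows from the stated rates. As 19.9 rounds to 20, there is almost no reserve: with hybrid at 83%, a control rate of 36% already gives 88.8%.

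**Step 2: vary the control rate.** Same formula, 20 per group, hybrid held at 83%:

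| Catheter success | Power | Per group for 90% |
|---|---|---|
| 35% (as planned) | 90.2% | 20 |
| 38% | 85.8% | 23 |
| 40% | 82.4% | 25 |
| 43% (own centre after redo, no drugs) | 76.6% | 29 |
| 46% (lower end of literature with redo and drugs) | 70.1% | 34 |

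For 43%: p̄ = 0.63, and power = Φ{(1.789 − 1.338)/0.621} = Φ(0.725) = 76.6%.

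**Step 3: check against exact enumeration.** Summing over all binomial outcomes with 20 per group, the uncorrected chi-square test has power 89.7% at 35% and 77.8% at 43%. Fisher's exact test has 83.2% and 67.7%. The choice of test thus matters at this size, which is why it should be named.

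**Step 4: how well does 43% fit?** It is the only post-redo rate without drugs in the article, but the series differs from the trial's catheter arm:

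- 54 of 70 patients (77%) had pulmonary vein isolation only; the trial requires a box lesion.
- Median follow-up was 21 months; the endpoint is at 12.
- No 6-month limit on the redo is reported; in the trial a later decision is a failure.
- Five of the 31 redo procedures were His bundle ablations, not repeat ablation of AF.

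The missing time limit would make 43% too high for the trial and the longer follow-up would make it too low. The net direction is unknown.

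**The case against.** The strongest reply is that 35% may already stand for the repeated strategy. The section says the estimate draws on literature and the centre's experience, its sentence defines success after the last procedure, and 35% lies between the centre's 21% and 43%. A true rate near 35% for the strategy is conceivable, and the cited sources cannot be checked here. But the text calls the figure a single-ablation rate and never argues that it covers the redo. It also lies inside the Discussion's single-procedure range (23–48%) and below its repeated-procedure range (46–69%).

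The second reply is that no post-redo figure in the article matches the trial. This stands, and it limits what can be said about size. If the 6-month limit keeps the catheter rate at 38–40%, power is still 82–86%.

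Two stronger readings are tempting and are not supported. A reader might carry the calculation to the top of the literature range, 69%, where power would be 17.5%. That range includes drug use, which the endpoint excludes, so it can serve only as an upper bound. A reader might also add the centre's 22-point redo gain (43 − 21) to 35%. That moves a gain seen from a lower baseline, with no stated time limit, onto a rate from other sources, and nothing in the article supports the sum.

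**Conclusion.** The point holds for the input, not the arithmetic. The 90% belongs to a comparison of one catheter ablation with hybrid ablation. The trial compares up to two catheter ablations with hybrid ablation. With hybrid at 83%, any catheter rate above about 35% takes power below 90%.

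The size of the shortfall is uncertain. At the nearest drug-free figure, 43%, the chance of missing the effect rises from about 10% to about 23%. This is illustrative, given the limits of that series. It assumes a hybrid rate of 83%, all 20 patients per group evaluable and a two-sided uncorrected chi-square test at 0.05. The article does not show that the trial lacks useful power; it shows that the stated power is not established for the comparison being made.

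**What to change.** In the sample size section:

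1. Replace the single-procedure rate with a justified rate for the catheter strategy as randomized: one or two ablations, the second decided within 6 months, without class I or III drugs.
2. State that 20 per group gives 90% power only if that rate is no higher than 35%, with hybrid at 83%.
3. Report power at 20 per group over a range such as 35–46%: about 90% at 35%, 86% at 38%, 82% at 40%, 77% at 43% and 70% at 46%.
4. Name the test and its sidedness.

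The change is to text only. Its cost is that the stated power becomes less favourable. Keeping a 90% claim at 43% against 83% would instead need 29 per group, 58 in total; restating the power does not require this.
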